**10.7 Clinical Management**

Adverse events will be managed by the clinical trial team who will assess and treat the event as appropriate, including referral to an independent physician and/or department. If any treatment/medical care is required as a result of the harm caused by the study vaccine or study procedures, this will be provided free of charge.

## **10.8 Pregnancy**

Although not considered an adverse event if a woman becomes pregnant during the study, it is the responsibility of the principal investigator or designee to report the pregnancy promptly using the same procedures for reporting SAEs. The pregnancy will be recorded on the appropriate source document. For follow up on a pregnancy refer to Section 12.1.1, Follow up After Discontinuation of Further Vaccination.

## **10.9 Intercurrent HIV Infection**

Though not considered an SAE, intercurrent HIV infection in study volunteers must be reported promptly using the same procedures for reporting SAEs.

HIV infection cannot be caused by the vaccine. Volunteers will be tested for HIV-1 and HIV-2 antibodies, as indicated in the Schedule of Procedures (Appendix A). HIV testing at additional time points may be performed at the discretion of the volunteer and Investigator, as medical or social circumstances arise.

## **11.0 MANAGEMENT OF HIV ISSUES DURING AND FOLLOWING THE TRIAL**

### **11.1 HIV Testing**

Only volunteers without HIV infection at screening will participate in the study. All HIV screening tests and routine post-vaccination tests will be performed by an independent laboratory that will follow a predetermined protocol to distinguish immune response to the vaccine from HIV infection. Results will be reported to the sites as HIV-infected or HIV-uninfected to prevent unblinding of the volunteer and staff. If a volunteer is found to be HIV-infected, a newly drawn blood specimen will be collected for confirmation.

Should a volunteer require an HIV test outside the study for personal reasons, it is recommended that the volunteer contact the study staff first. The HIV test may be drawn at the clinical site and then processed at the independent laboratory as above. Written evidence of HIV status (infected or not infected) will be provided to the volunteer upon request.

### **11.2 HIV Infection**

Volunteers who are found to be HIV infected at screening and study volunteers who acquire HIV infection during the trial will be managed in the following way:

#### **11.2.1 Counseling**

The volunteer will be counselled by the study counsellors. The counseling process will assist the volunteer with the following issues:

- Psychological and social implications of HIV infection

- Whom to inform and what to say
- Implications for sexual partners
- Avoidance of transmission to others in future

### **11.2.2 Referral for support and/or care**

Volunteers will then be referred to a patient support centre or institution of his/her choice for a full discussion of the clinical aspects of HIV infection. Referral will be made to a designated physician or centre for discussion of options of treatment of HIV-infection.

### **11.3 Social Discrimination as a Result of an Antibody Response to Vaccine**

The aim is to minimize the possibility of social discrimination in volunteers who develop vaccine-induced antibodies and therefore test positive on a routine ELISA test by providing appropriate diagnostic HIV testing and certification for volunteers as required, outlined above, both during and after the trial. In addition, a letter stating that the individual has participated in a vaccine trial, giving a contact number in case of medical emergency will be provided.

## **12.0 DISCONTINUATION OF VACCINATION AND/OR VOLUNTEER WITHDRAWAL FROM STUDY**

### **12.1 Discontinuation of Further Vaccinations**

Volunteers will be discontinued from further vaccination for any of the following reasons:

1. A disease or condition or an adverse event that may develop, regardless of relationship to the candidate vaccine, if the principal investigator or designee is of the opinion that further vaccination will jeopardize the safety of the volunteer.
2. An abnormal laboratory event based on the following criteria, defined in Section 10.6:
  - For a mild laboratory event, volunteers may be vaccinated only if the abnormality is judged to be not clinically significant by the principal investigator or designee,
  - For a moderate laboratory event, the laboratory test must be repeated and the event determined to be resolved in the opinion of the principal investigator or designee prior to vaccination,
  - For a severe or very severe laboratory event, even if resolved, the IAVI Medical Affairs Expert must be consulted before making a decision to vaccinate.
3. A severe local reactogenicity event involving the major circumference of the arm, not resolving within 72 hours.
4. Anaphylaxis; bronchospasm; laryngeal oedema; collapse; convulsions or encephalopathy.
5. Life threatening medical event following vaccination unless not related to the investigational product.

6. Any immediate hypersensitivity reaction judged due to investigational product.
7. Pregnancy.
8. Intercurrent HIV Infection.
9. Volunteer request to discontinue further vaccination.

Any volunteer discontinuing further vaccination or being considered for discontinuation of vaccine will be discussed with the IAVI Medical Affairs Expert.

#### **12.1.1 Follow up after discontinuation of further vaccinations**

Any adverse event resulting in the discontinuation of a volunteer's vaccinations will be followed up until resolution or until the adverse event is judged by the principal investigator or designee to have stabilized where possible. Immunological monitoring will continue, provided the volunteer is willing. The frequency of assessments will be determined by the Trial Steering Committee.

A pregnant volunteer will be followed until the end of the study and until delivery, if delivery occurs after the study has ended. Approximately 2-4 weeks after delivery, the baby will be examined by a pediatrician to assess the health status of the baby. The health status of the baby will be reported to IAVI.

Follow-up of HIV-infected individuals who have received investigational product will be determined by the Trial Steering Committee.

The date and reason for discontinuation of vaccination should be collected.

#### **12.2 Withdrawal from the Study (Early Termination)**

Volunteers may be withdrawn from the study permanently for the following reasons:

1. Volunteers may withdraw from the study at any time if they wish to do so, for any reason.
2. Following an adverse event at the discretion of the investigator (or designee) discretion.
3. The principal investigator or designee has reason to believe that the individual is not complying with the protocol.

##### **12.2.1 Follow up after withdrawal from study (Early Termination)**

Any adverse event resulting in the withdrawal of a volunteer will be followed up until resolution or until the adverse event is judged by the principal investigator or designee to have stabilized where possible.

At the time of the withdrawal, provided the volunteer is willing, all the requested termination visit procedures will be performed according to the Schedule of Procedures (Appendix A).

The date and reason for withdrawal from the study (early termination) should be collected. Volunteers who are withdrawn from the study (early termination) will not be replaced, but, wherever possible, will be followed up to the time of their final planned visit.

## **13.0 DATA HANDLING**

### **13.1 Data Handling at the Trial Sites**

Data will be collected by the clinical trial staff and entered on to the appropriate source document.

All source documents and laboratory reports will be reviewed by the clinical team and the data entry clerk, who will ensure that they are accurate and complete. Adverse events will be graded, assessed for severity and causality and reviewed by the principal investigator or designee as they arise.

Changes to source documents must be initialled and dated and the reason for change must be noted. All source documents will be kept in a secure location and held for 15 years. The written records for the trial will be held at the site.

### **13.2 Data Collection and Transfer at the IAVI Core Laboratory**

Data generated at the IAVI Core Laboratory will be transferred directly to the Data Coordinating Center (the EMMES Corporation)

### **13.3 Data Entry at the Trial Sites**

Data will be entered into the EMMES Internet-based Data Entry System (IDES). Consistency checks and range checks will be performed by data entry and supervisory personnel. Queries raised by the monitor or by The EMMES Corporation will be directed to the investigators and study staff. A file will be held at the clinic(s) for each local volunteer containing all the source documents and written documentation on all queries raised and how they were addressed.

### **13.4 Quality Assurance and Audit**

To ensure the quality and reliability of the data gathered and the ethical conduct of this trial, standard operating procedures have been developed for all clinic and laboratory procedures. Regular monitoring and an independent audit of the trial will be performed according to Good Clinical Practice (GCP).

### **13.5 Data Handling and Analysis**

The statistician at the Data Coordinating Center (EMMES Corporation), in collaboration with the principal investigators (or designees) and the sponsor, will create tables according to a data analysis plan that has been reviewed and agreed to by the principal investigators (or designees) and IAVI. The EMMES Corporation will conduct the data analysis and will provide interim and final study reports for the DSMB, IAVI, principal investigators (or designees) and the regulatory authorities as appropriate. Prior to an

analysis, additional monitoring visits will take place if necessary to validate the data held on the database, as well as all consent forms and dispensing records. Data files will be prepared by EMMES from a 'frozen' dataset for that particular analysis.

Unblinded data will be seen only by the DSMB prior to unblinding the trial. Preliminary grouped data analyses may be done without unblinding of volunteers, principal investigators, laboratory personnel, or IAVI to individual assignments.

### 13.6 Trial Supervision and Monitoring

The Data and Safety Monitoring Board (DSMB) and the Trial Steering Committee (TSC) will oversee the progress of the clinical trial.

The clinical study monitor will ensure that the trial is conducted, recorded and reported in accordance with the protocol, standard operating procedures, Good Clinical Practice (GCP), ICH Guidelines and the applicable regulatory requirements. The monitor will validate trial data held on the database against the source documents. The principal investigator, by signing the protocol, and the volunteers, by giving consent, agree that the monitor may consult and/or copy source records (clinical notes, laboratory values and other medical records if applicable) to accomplish this task. Such information will be treated as strictly confidential and will under no circumstances be made publicly available. The monitoring will adhere to Good Clinical Practice and ICH guidelines. Data that should be verifiable from source documents for trial volunteers include, but are not limited to:

- Documentation of any existing conditions or past conditions relevant to eligibility
- Signed consent forms
- Dates of visits including dates of vaccinations
- Reported laboratory results
- All adverse events
- Concomitant medications

## 14.0 STATISTICAL CONSIDERATIONS

### 14.1 Sample Size

The study uses a dose-escalation design of ADVAX e/g + ADVAX p/n-t vaccine candidate or placebo administered intramuscularly three times during the course of the study. The study investigates three dose levels of ADVAX e/g + ADVAX p/n-t vaccine, 0.2 mg, 1 mg, and 4 mg. Each dose group consists of 15 volunteers randomized in a 4:1 ratio of active vaccine to placebo.

A total of up to 45 volunteers will be enrolled in the study; 36 volunteers will be given active vaccines and 9 volunteers will be given placebo. The small sample size is appropriate for an exploratory dose-escalation study of a novel product while safety and tolerability and immunogenicity of the vaccine are investigated.

### 14.2 Statistical Power and Analysis

#### ***Vaccine Safety and Tolerability:***

The rate of local and systemic reactogenicity events will be used to assess the differences between dose groups. The sample size of the study was restricted by safety

considerations. Nevertheless, the study has at least 80% power (at  $\alpha=0.05$  confidence level of an exact one-sided trend test) to detect the difference of 48 percentage points or more in the rate of events between the active ( $n_1=36$ ) and the placebo ( $n_2=9$ ) groups. The power of the statistical comparison was computed assuming 10% rate of events in the placebo group.

The rate of Serious Adverse Events related to vaccine will be used as one measure of the safety of the candidate vaccine. Adverse Events that may be temporarily incapacitating (for example, loss or cancellation of work or social activities), which could make a vaccine impractical for large scale use if they occur in more than a small proportion of cases, will also be assessed.

All adverse events will be reported, grouped as to whether or not they qualify as SAEs, their severity assessment, and their relationship to vaccine (as judged by the investigator and reviewed by the sponsor and the DSMB). The following example illustrates the limited statistical power of this initial Phase 1 study.

*Prior to the enrollment of the medium dose level group:*

If none of the volunteers receiving the vaccine experiences an SAE related to vaccine ( $n=12$ ), the 95% upper confidence bound for the rate of these adverse events in the population is 0.22.

*Prior to the enrollment of the highest dose level group:*

If none of the volunteers receiving the vaccine experiences an SAE related to vaccine ( $n=24$ ), the 95% upper confidence bound for the rate of these adverse events in the population is 0.12. Restricted to the medium dose level group ( $n=12$ ), the upper confidence bound would be 0.22.

*After completion of the study:*

If none of the volunteers receiving the vaccine experiences an SAE related to vaccine ( $n=36$ ), the 95% upper confidence bound for the rate of these adverse events in the population is 0.08. Restricted to the two highest dosage level groups ( $n=24$ ), the upper confidence bound would be 0.12. Restricted to the highest dose level group ( $n=12$ ), the upper confidence bound would be 0.22.

***Vaccine Immunogenicity:***

Cellular immune responses will be analyzed using binomial methods to examine for the presence or absence of HIV-specific T-cell responses quantified by ELISPOT and cytokine flow cytometry (CFC). Presence or absence of binding and neutralizing antibodies will be also analyzed. Assays will be performed in a similar fashion in all volunteers. Because of the small sample sizes and multiple epitopes, the results will be primarily descriptive. Nevertheless, the study has at least 80% power (at  $\alpha=0.05$  confidence level of an exact one-sided trend test) to detect the difference of 45 percentage points or more in the response rate between the active ( $n_1=36$ ) and the placebo ( $n_2=9$ ) groups. The power of the statistical comparison was computed assuming 5% response rate in the placebo group. The study has at least 80% power (at  $\alpha=0.05$  confidence level of an exact one-sided trend test) to detect the difference between the response rates of 20% and 72% in any two dose groups ( $n_1= n_2=12$ ).

Based on the previous experience with IAVI Phase I vaccine studies, it is expected that the amount of missing, unused or spurious data will be insignificant. Unused and spurious data will be listed separately and excluded from the statistical analysis. Missing

data will be excluded from the statistical analysis. A data analysis plan will be developed and agreed upon by IAVI and the investigators prior to unblinding.

## **15.0 DATA AND BIOLOGICAL MATERIAL**

All data and all biological material collected through the clinical trial shall be the joint property of the principal investigators or designees and IAVI.

The raw computerized data generated in this study will be held by the EMMES Corporation on behalf of IAVI and the principal investigators or designees. The clinical sites will also hold the frozen data files and tables generated for the purposes of analysis. Principal investigators or designees will have access to the EMMES database with appropriate blinding.

## **16.0 ADMINISTRATIVE STRUCTURE**

The principal investigator will be responsible for all aspects of the trial at the study site.

### **16.1 Trial Steering Committee (TSC)**

The supervision of the trial and the operational activities will be the responsibility of a Trial Steering Committee (TSC) consisting of the principal investigators and designees, and sponsor representatives. The TSC will meet regularly with representatives from the clinical, laboratory and data management teams.

### **16.2 Data and Safety Monitoring Board (DSMB)**

The DSMB will consist of independent individuals who are not involved in the trial. No investigators responsible for the clinical care of trial volunteers or representative of IAVI may be a member of the DSMB. However, the DSMB may invite the principal investigators or designees and an IAVI representative to an open session of the meeting to provide information on study conduct, present data or to respond to questions at an open portion of the DSMB meeting.

The review of trial data by the DSMB will take place at least 14 days after the tenth volunteer in each dose group receives the second injection before proceeding to the next dose group. Additional meetings will take place if there are indications for an interim review, which may be unblinded at the discretion of the DSMB.

#### **16.2.1 Content of interim review**

The DSMB will be asked to review on an interim basis:

- All severe or very severe clinical adverse/reactogenicity events judged by the principal investigator or designee to be possibly, probably or definitely related to vaccine.
- All severe or very severe laboratory adverse events confirmed on retest and judged by the principal investigator or designee to be possibly, probably, or definitely related to vaccine.

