## 5.0 STUDY DESIGN AND ENDPOINTS

### 5.1 STUDY ENDPOINTS

#### 5.1.1 Primary Endpoints

Safety and Tolerability:

- Severe and very severe local reactogenicity events (pain, tenderness, erythema/skin discoloration, skin damage [vesiculation/ulceration], induration, formation of crust or scab)
- Severe and very severe systemic reactogenicity events (fever, chills, headache, nausea, vomiting, malaise, myalgia)
- Severe and very severe other adverse events (including laboratory abnormalities)
- All Serious Adverse Events
- Proportion of volunteers with mild and moderate local and systemic reactogenicity events and adverse events

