### 5.2 STUDY DESIGN

The study is a randomized, dose-escalating, double blind (with respect to active vaccine or placebo), placebo-controlled study.

Safety and tolerability of the ADVAX e/g + ADVAX p/n-t vaccine/placebo will be evaluated at least 14 days after the tenth volunteer in the lower dosage group receives the second injection before proceeding to the middle dosage group. Likewise, there will be an evaluation at least 14 days after the tenth volunteer in the middle dosage group receives the second injection before proceeding to the higher dosage group.

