#### 10.4 Relationship to Study Product

The determination of the likelihood that the investigational product caused the (serious) adverse event will be provided by an investigator who is a qualified physician. The investigator must sign and date the source document that supports the causality.

The criteria below are intended as a guideline to assist the investigator in determining causality (not all criteria must be present):

**Not Related:** This category applies to those (S)AEs that, after careful medical consideration, are clearly felt to be due to extraneous causes (disease, environment, etc.) unrelated to the vaccine under investigation.

**Unlikely:** This category applies to those adverse events that, after careful medical consideration, are considered unlikely to be related to the trial vaccine with near certainty. In general, this category is applicable to an (S)AE that meets the following criteria:

1. It does not follow a reasonable temporal (time) sequence from administration of the vaccine.
2. It may have been readily produced by the volunteer's clinical state, environmental or toxic factors, or other modes of therapy administered to the volunteer.
3. It does not follow a known pattern of response to the vaccine.

**Possibly:** This category applies to those adverse experiences that, after careful medical consideration, are felt unlikely to be related to the vaccine although the possibility cannot be ruled out with certainty. An (S)AE may be considered possibly related if, or when:

1. It follows a reasonable temporal (time) sequence from administration of the vaccine.
2. It may have been produced by the volunteer's clinical state, environmental or toxic factors, or other modes of therapy administered to the volunteer.
3. It follows a known pattern of response to the vaccine.

**Probably:** This category applies to those adverse experiences that, after careful medical consideration, are felt with a high degree of certainty to be related to the trial vaccine. An (S)AE may be considered probably related, if:

1. It follows a reasonable temporal (time) sequence from administration of the vaccine.
2. It cannot be reasonably explained by the known characteristics of the volunteer's clinical state, environmental or toxic factors, or other modes of therapy administered to the volunteer.
3. It follows a known pattern or response to the suspected vaccine.
4. It reappears after administration of an additional dose of vaccine, if given.

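### The DSMB's review list is filtered by blinded attribution and by retest, so some primary-endpoint events need not be before it when the dose is raised

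*Protocol*

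**What the plan says.** Section 16.2 makes a DSMB review the gate to each higher dose, timed from dose two of the schedule. The sentence opens "The review of trial data by the DSMB will take place at least 14 days after the tenth volunteer in each dose group receives the" and goes on to name that dose. Section 5.2 gives the purpose of the gate in broad terms: "Safety and tolerability of the ADVAX e/g + ADVAX p/n-t vaccine/placebo will be evaluated" before the study moves to the next dosage group.

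Section 16.2.1 is the only statement of what the DSMB is asked to look at. It has two entries. The clinical entry is "All severe or very severe clinical adverse/reactogenicity events judged by the principal investigator or designee to be possibly, probably or definitely related to vaccine". The laboratory entry opens "All severe or very severe laboratory adverse events confirmed on retest and judged by the principal investigator or designee to be possibly, probably, or definitely", and so adds the retest to the same attribution condition.

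The primary endpoints in 5.1.1 are wider. They cover severe and very severe local and systemic reactogenicity, "Severe and very severe other adverse events (including laboratory abnormalities"), all SAEs, and the proportion of volunteers with mild and moderate events. None of these depends on attribution or retest.

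Section 10.4 sets the attribution scale. *Unlikely*, which falls outside the filter, is for events "considered unlikely to be related to the trial vaccine with near certainty". *Possibly*, which falls inside it, is for events "felt unlikely to be related to the vaccine although the possibility cannot be ruled out with certainty".

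**The concern.** The decision to raise the dose appears to rest on a narrower set of events than the endpoint the trial is meant to report. The narrowing is done by staff who, under 8.7, do not know whether the volunteer had vaccine or placebo, and who judge one case at a time. Section 13.5 says that only the DSMB sees unblinded data before the trial is unblinded. It is the one body that could set events against arm, yet the list it is given has already been cut by people who cannot.

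The laboratory entry adds a second cut. Under 9.1.4 a further sample after an abnormal value is at the investigator's discretion, so a severe value that is not repeated, or that has settled when it is, drops off the list.

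The attribution cut-point is also soft, because the wording on both sides of it describes a relationship thought unlikely. Two careful investigators could place the same event on opposite sides.

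**Working it through.** **1. The review list against the primary endpoints**

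| Event type | Primary endpoint (5.1.1) | DSMB list (16.2.1) | Other stated route to the DSMB |
|---|---|---|---|
| Severe clinical, judged at least *Possibly* related | yes | yes | not needed |
| Severe clinical, non-serious, judged *Unlikely* or *Not Related* | yes | no | none with a time point |
| Severe laboratory, confirmed on retest and judged related | yes | yes | not needed |
| Severe laboratory, non-serious, not confirmed on retest | yes | no | none with a time point |
| Mild or moderate reactogenicity | yes | no | none with a time point |
| SAE, any attribution | yes | not as such | 10.6: the sponsor notifies the DSMB |

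(Severe here includes very severe.) The gap is rows 2, 4 and 5. Row 6 is covered.

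**2. The cut-point in 10.4**

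- The lead sentences of *Unlikely* and *Possibly* both call the event unlikely to be related. They differ in the degree of certainty expressed.
- The second criterion, on other possible causes, is nearly the same in both.
- The first criterion, on timing, is opposite: a plausible interval from injection points to *Possibly* and an implausible one to *Unlikely*.

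So timing does separate the categories, but the lead sentences do not do so cleanly. An event can cross in either direction. Read literally, *Possibly* is set low and would send more events to the DSMB.

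**3. The plan's own bounds**

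Section 14.2 gives 95% upper bounds for zero related SAEs of 0.22, 0.12 and 0.08 at n = 12, 24 and 36. The one-sided exact bound is 1 − 0.05^(1/n):

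- n = 12: 0.221
- n = 24: 0.117
- n = 36: 0.080

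All three reproduce, so the same one-sided convention is used below.

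**4. Illustration at the gate**

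The documents give no expected rate of severe events and no rate of attribution. The number of vaccinees among the first 10 of a 12:3 group is expected to be 10 × 12/15 = 8 and can be 7 to 10. If the order within the 15 is fully random, the probabilities of 7, 8, 9 and 10 are 0.26, 0.49, 0.22 and 0.02.

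The upper bound for x events in 8 is the p that solves P(X ≤ x | 8, p) = 0.05:

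- 0/8: 31%
- 1/8: 47%
- 2/8: 60%

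For zero events the bound is 35% with 7 vaccinees and 26% with 10.

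Now let p be the assumed share of vaccinees with a non-serious severe event and s the assumed chance that such an event gets onto the list. With one event per vaccinee and independence, the chance that at least one occurs but none is listed is (1 − ps)^8 − (1 − p)^8:

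| p | s = 0.75 | s = 0.50 | s = 0.25 |
|---|---|---|---|
| 0.10 | 0.105 | 0.233 | 0.386 |
| 0.20 | 0.105 | 0.263 | 0.496 |
| 0.30 | 0.072 | 0.215 | 0.478 |

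These figures show how sensitive a group of 8 is to one label. They do not estimate what will happen.

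**The case against.** Several things soften the point, and most of them stand.

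- **The list is not the DSMB's only source.** A reader might infer that SAEs called unrelated are hidden. They are not: 10.6 has the sponsor notify the DSMB of SAEs with no causality condition. Section 14.2 says that relationship is reviewed by the sponsor and the DSMB, and 13.5 provides for interim reports to the DSMB. However, 14.2 gives no time point and 13.5 no content. The full safety data are promised only in 16.2.2, after three or more volunteers have a related SAE.
- **Section 16.2.1 may not govern the escalation reviews.** Section 16.2 attaches the term interim review to additional meetings, and 16.2.1 says what the DSMB will be asked to review, not the most it may see. That is a real ambiguity. If 16.2.1 does not apply, the protocol states no content for the escalation reviews at all, which also needs mending.
- **A bias toward under-reporting is not shown.** A reader might argue that a new product has no known response pattern, so that criterion pushes events toward *Unlikely*. The text does not support this. The criteria in 10.4 are a guideline and need not all be met, Appendix C lists expected vaccination reactions, and 3.1.4 describes reactions to other DNA vaccines. The timing criterion would send a severe event soon after injection to the DSMB.
- **An interim list need not mirror the final endpoint.** True, and the difference alone would be no error. What matters is that the filter is a judgement made blind to arm, applied before the only unblinded reader. With about 8 vaccinees and 2 placebo recipients at the first gate, an arm comparison would be weak in any case, so the main gain is a complete count.

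**Conclusion.** The point holds in a limited form. As written, the list that appears to inform both escalation decisions leaves out three kinds of primary-endpoint event: non-serious severe or very severe events judged unrelated or unlikely, severe laboratory events not confirmed on retest, and mild or moderate reactogenicity. The boundary between *Unlikely* and *Possibly* is loose and can shift events either way.

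This rests on reading 16.2.1 as applying to the escalation reviews, which is the natural reading because no other content is given. The documents do not support saying that the DSMB sees nothing else, that SAEs are withheld, or that the net effect is to hide harm.

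The size cannot be derived from the protocol. The bounds of 31%, 47% and 60% illustrate only that one or two labels matter in a group of about 8. The protocol should be corrected, preferably before the first escalation review, but this does not invalidate the design.

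**What to change.** 1. In 16.2.1, state that it applies to the escalation reviews in 16.2 as well as to any additional meeting.
2. Replace the two entries with a list that the DSMB receives by dose group and coded arm, with denominators: all SAEs; all severe and very severe clinical and laboratory events, whatever the attribution or retest result; and a summary of reactogenicity by maximum grade. Show the investigator's attribution and the retest result as columns.
3. Reconcile this with 14.2 by saying when the DSMB reviews relationship.
4. In 10.4, reword *Possibly* so that it no longer shares its lead description with *Unlikely* and the categories are mutually exclusive, for example as a causal relationship that cannot be excluded.

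The cost is amendment wording and a few more rows in reports that the data centre already prepares for the DSMB under 13.5. No dose, escalation threshold or stopping rule is changed.
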